# Forced fluid removal versus usual care in intensive care patients with high-risk acute kidney injury and severe fluid overload (FFAKI): study protocol for a randomised controlled pilot trial

**DOI:** 10.1186/s13063-017-1935-2

**Published:** 2017-04-24

**Keywords:** Acute kidney injury, Fluid, Fluid overload, Intensive care, Randomised trial, Feasibility trial

## Abstract

**Background:**

Intravenous administration of fluids is an essential part of critical care. While some fluid administration is likely beneficial, there is increasing observational evidence that the development of fluid overload is associated with increased mortality. There are no randomised trials to confirm this association in patients with acute kidney injury. We aim to perform a pilot trial to test the feasibility of forced fluid removal compared to standard care in patients with acute kidney injury and severe fluid overload, the FFAKI trial.

**Methods:**

Then FFAKI trial is a pilot, multicentre, randomised clinical trial recruiting adult intensive care patients with acute kidney injury and fluid overload, defined as more than 10% of ideal bodyweight. Patients are randomised with concealed allocation to either standard care or forced fluid removal with a therapeutic target of negative net fluid balance ≥1 mL/kg/h. The safety of fluid removal is continually evaluated according to predefined criteria of hypoperfusion: lactate ≥4 mmol/L, mean arterial pressure <50 mmHg or mottling beyond the edge of the kneecaps. If patients fulfil one of these criteria, fluid removal is suspended until hypoperfusion has resolved. The primary outcome measure is fluid balance at 5 days after randomisation and secondary outcomes include mean daily fluid balance, fluid balance at discharge from the intensive care unit, time to neutral fluid balance, number of serious adverse reactions and number of protocol violations. All patients are followed for 90 days.

**Discussion:**

The FFAKI trial started in October 2015 and, when completed, will provide data to evaluate whether a large trial of forced fluid removal in critically ill patients is feasible. Our primary outcome will show if the experimental intervention leads to a clinically relevant difference in fluid balance, which could prove beneficial in intensive care patients with acute kidney injury.

**Trial registration:**

EudraCT, identifier: 2015-001701-13. Registered on 19 September 2015;

ClinicalTrials.gov, identifier: NCT02458157. Registered on 21 May 2015;

Danish Ethics Committee, identifier: H-15009589H. Registered on 22 September 2015; Danish Health and Medicines Authority, identifier: 2015070013. Registered on 11 August 2015.

**Electronic supplementary material:**

The online version of this article (doi:10.1186/s13063-017-1935-2) contains supplementary material, which is available to authorized users.

## Background

Administration of isotonic crystalloid solutions is a common intervention in critically ill patients. In some cases this leads to the accumulation of fluids and development of fluid overload, defined as a positive fluid balance corresponding to 10% or more of total bodyweight. The cut-off at 10% was first utilised in a paediatric observational study by Gillespie et al. [1], and subsequently adopted in the adult population [2]. Growing observational data have linked fluid overload to a poor outcome in several different patient populations including those with acute kidney injury (AKI) [3]. This was analysed in a recent systematic review and meta-analysis of data from 12 cohort studies including 5095 patients [4]. Six of the 12 studies reported adjusted odds ratios (ORs) for death, and the pooled results associated fluid overload with increased risk of death with an OR of 2.23 (95% CI, 1.66–3.01) and a moderate level of heterogeneity (*I*
^*2*^ = 62%). Mean positive daily fluid balance was also shown to be associated with death with an OR of 1.16 (95% CI, 1.07–1.27); however, there was significant heterogeneity amongst the studies (*n* = 6, *I*
^*2*^ = 94%).

The observed association between fluid overload and outcome may in part be mediated by the development of interstitial oedema leading to deranged organ architecture, increased diffusion distances for oxygen and metabolites and increased interstitial pressure [5].

A study in healthy volunteers demonstrated that infusion of 2 L crystalloid leads to renal swelling [6]. Renal interstitial volume and pressure may be correlated in a nonlinear manner, suggesting that a ‘renal compartment’ exists [7] and increased interstitial pressure has been linked to a decline in renal blood flow (RBF), glomerular filtration rate (GFR) and sodium excretion [8, 9]. The detrimental effect of fluid overload has been attenuated in experimental renal decapsulation in both animals and humans [10].

Given the observational nature of the available data, there is a high risk of confounding by indication and a causal relationship cannot be established before randomised data are available [11]. We aim to perform a feasibility trial of forced fluid removal in intensive care unit (ICU) patients with AKI and severe fluid overload. If we are able to achieve a clinically relevant difference in fluid balance we believe that a definitive trial powered for mortality is warranted.

## Methods

The FFAKI trial is a multicentre, randomised, site-stratified, clinical pilot trial with adequate computer generation of the allocation sequence with permuted blocks of varying size and allocation concealment. Randomisation is performed using sequentially numbered, opaque, sealed envelopes.

The trial statistician is blinded but due to the nature of the intervention it is not possible to blind patients or caregivers.

The trial is initiated at three separate centres in Denmark. Each centre has one or two primary investigators with expert knowledge in the FFAKI intervention and protocol. Participants in the FFAKI trial will receive protocol-specific treatment during their entire ICU stay. Therefore, every caregiver at participating centres receives training in the protocol by either the principal investigator or one of the primary investigators. It is expected that the primary centre (Nordsjællands Hospital) will include 20–30 patients and each secondary centre will include 10–15 patients.

The trial protocol was written according to the Standard Protocol Items: Recommendations for Interventional Trials (SPIRIT) Statement [12]. A populated SPIRIT Checklist and figure are provided in Additional file 1 and Fig. 1, respectively.

**Fig. 1 Fig1:**
[figure not shown]
Standard Protocol Items: Recommendations for Interventional Trials (SPIRIT) figure for the FFAKI trial. CONSORT 2010 Flow Diagram for the FFAKI-trial

### Patients

All patients admitted to the ICU at the participating centres will be eligible for screening according to the following:

#### Inclusion criteria

Age 18 years or olderAKI defined according to the Kidney Disease Improving Global Outcomes (KDIGO) criteria [13]Renal Recovery Score (RRS) ≤60%Fluid overload defined as a positive fluid balance of at least 10% of ideal body weightAble to undergo randomisation within 12 h of fulfilling the other inclusion criteria

#### Exclusion criteria

Known allergy to furosemide or sulphonamidesKnown prehospitalisation advanced chronic kidney disease (estimated glomerular filtration rate (eGFR) <30 mL/min/1.73 m^2^ or chronic renal replacement therapy)Severe hypoxic respiratory failure (use of invasive ventilation and fraction of inspired oxygen (FiO_2_) >80% and positive end-expiratory pressure (PEEP) >10 cmH_2_O)Severe burn injury (≥10% total burned surface area)Severe dysnatraemia (plasma concentrations <120 or >155 mmol/L)Hepatic comaMentally disabled undergoing forced treatmentPregnancy/breastfeedingLack of commitment for ongoing life support including renal replacement therapy (RRT)Lack of informed consent

Patients who fulfil all of the inclusion criteria and none of the exclusion criteria will be enrolled in the trial and allocated to either the experimental treatment (forced fluid removal) or standard care. Based upon own observational data we expect that roughly 10% of adult patients admitted for more than 24 h will be available for inclusion in the FFAKI trial (Fig. 2).

**Fig. 2 Fig2:**
[figure not shown]
Consolidated Standards of Reporting Trials (CONSORT) diagram

### Forced fluid removal (Figs. 3, 4 and 5)

**Fig. 3 Fig3:**
[figure not shown]
FFAKI algorithm for fluid removal with furosemide

**Fig. 4 Fig4:**
[figure not shown]
FFAKI algorithm for fluid removal with continuous renal replacement therapy (CRRT)

**Fig. 5 Fig5:**
[figure not shown]
FFAKI resuscitation algorithm

The experimental intervention is guided by a therapeutic goal of average net negative fluid balance ≥1 mL/kg/h and safety variables indicating inadequate circulation (lactate ≥4 mmol/L or mean arterial pressure (MAP) <50 mmHg or mottling beyond the edge of the kneecaps).

The therapeutic effect is evaluated at three daily summary points on the ICU observation charts (06:00, 14:00 and 22:00), while safety variables are evaluated continuously.

The first choice for fluid removal is diuretic therapy with furosemide which is continued for a minimum of 8 h. If the therapeutic goal cannot be achieved and maintained by diuretic therapy it is replaced by fluid removal with continuous renal replacement therapy (CRRT).

### Resuscitation

During the entire trial, the physiologic response to fluid removal is monitored with three variables indicating inadequate circulation. These are:Mottling beyond the edge of the kneecaps [14]Hypotension (MAP <50 mmHg) resistant to inotropes and vasopressorsPlasma lactate ≥4 mmol/L [15]

Mottling and MAP are monitored continuously and lactate is routinely measured four to six times each day and on clinical indication.

If one or more signs of inadequate circulation are present the resuscitation algorithm is started:Pause fluid removalGive a crystalloid fluid bolus of 250–500 mLRe-evaluate circulatory status within 30 minRepeat fluid therapy and revaluation until adequate circulation (lactate <4 mmol/L, MAP >50 mmHg and no mottling beyond kneecaps) have been maintained for minimum 1 hRestart fluid removal in 25% reduced dose for a minimum of 4 h before evaluating effect

Fluid removal is continued until the patient achieves neutral cumulative fluid balance (±1000 mL), which is then attempted maintained for the entire duration of ICU admission.

### Standard care

In the control group receiving standard care, there are no protocolled interventions. Fluid administration and removal is done at the discretion of the treating clinicians. Use of dialysis is encouraged only in the presence of severe disturbances in fluid, electrolyte and acid-base balance:Hyperkalaemia (p-K^+^ >6 mmol/L)Severe metabolic acidosis attributable to AKI (pH <7.25 and standard base excess (SBE) below −10 mmol/L) resistant to intravenously (IV) administered bicarbonate infusionSevere respiratory failure with PaO^2^/FiO^2^ < 13 kPa and bilateral infiltrates/oedema on the chest X-rayAside from these absolute indications, RRT may be provided in case of progressive azotaemia and blood urea (BUN) >25 mmol/L

All data are collected in a paper-based Case Research Form (CRF) and participants are followed for a total of 90 days. The primary outcome of the FFAKI trial is cumulative fluid balance 5 days after randomisation. All outcome variables are shown in Table 1. Furthermore, we will evaluate the safety of the intervention by registering known serious adverse reactions (SARs) to furosemide and serious adverse events (SAEs) to fluid removal including: arrhythmia, ischaemia, vasopressor use and progression of organ failure as captured in the daily Sequential Organ Failure Score (SOFA) score.

**Table 1 Tab1:** Primary, secondary and exploratory outcomes for the FFAKI trial

Primary outcome	Cumulative fluid balance 5 days after randomisation
Secondary outcomes	Mean daily fluid balance during ICU stay
	Cumulative fluid balance during the entire ICU stay
	Time to neutral cumulative fluid balance
	Number of patients with one or more major protocol violations
	Accumulated SARs in each intervention arm during the ICU stay
Exploratory outcomes	All-cause mortality at day 90
	Days alive and out of hospital within 90 days of follow-up
	Days alive without mechanical ventilation within 90 days of follow-up
	Days alive without vasopressor/inotropic therapy within 90 days follow-up
	Days alive without RRT within 90 days follow-up
	Renal recovery at day 90

*ICU* intensive care unit, *RRT* renal replacement therapy, *SAR* serious adverse reaction

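### Three secondary outcomes run over each patient's own ICU stay, so a difference between arms in length of stay or ICU deaths can shift them even when fluid removal is identical

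*Protocol article*

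**What the plan says.** Table 1 of the protocol article (under Standard care) defines three secondary outcomes over the ICU stay: "Mean daily fluid balance during ICU stay", "Cumulative fluid balance during the entire ICU stay" and "Accumulated SARs in each intervention arm during the ICU stay". The Abstract describes the second as "fluid balance at discharge from the intensive care unit".

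Other outcomes in the same table have fixed windows. The primary outcome is "cumulative fluid balance 5 days after randomisation". The exploratory outcomes are set at or within 90 days, which matches the statement that "participants are followed for a total of 90 days".

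Treatment runs as long as the ICU stay: "Participants in the FFAKI trial will receive protocol-specific treatment during their entire ICU stay". Under Resuscitation, removal continues to a neutral cumulative balance (±1000 mL), "which is then attempted maintained for the entire duration of ICU admission".

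The Statistical analysis section describes two analyses that address death, a linear random-effects model and a survivor average causal effect, both with inverse probability weighting for dropout. It assigns them to the primary outcome. For other continuous data it names Student's t test or the Mann-Whitney U test.

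**The concern.** The window is decided after randomisation, by ICU death or discharge. Both may respond to treatment, and both may be unbalanced by chance in a trial of 50. Three mechanisms follow.

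- **Mean daily balance.** After neutral is reached and held, each further ICU day adds about nothing to the numerator and one day to the denominator. Longer stays pull the mean towards zero.
- **Cumulative balance.** A stay that ends before neutral, by death or discharge, freezes the balance part-way. Shorter stays leave it higher.
- **Accumulated SARs.** An arm total with no exposure time beside it tends to follow the time at risk. An arm with earlier deaths can show fewer SARs.

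A plain two-sample test on either fluid outcome compares windows of unequal length. At stake is how the secondary fluid and safety results are read when a larger trial is considered.

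**Working it through.** **1. The plan's own figure.** Inputs from Statistical analysis: difference 6 L, SD 7.4 L, 80% power (printed there as a β value), two-sided α 0.05. Equal allocation is assumed, since the article gives no ratio.

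n per arm = 2 × (1.960 + 0.842)² × 7.4² / 6² = 23.9, so 24 per arm and 48 in total. The t-based version gives 24.9, so 25 per arm and 50 in total, with power 0.802. The planned 50 is reproduced. It rests on the day-5 outcome and is not touched by this point.

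**2. One removal course, different stays.** Assumptions: weight 80 kg; a starting balance of 13.8 L (the planning mean, whose time point is not stated); removal at exactly the stated target of 1 mL/kg/h until zero, then flat; daily mean counted from randomisation.

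- Rate = 1 × 80 × 24 / 1000 = 1.92 L/day. Time to zero = 13.8 / 1.92 = 7.2 days (9.6 days at 60 kg, 6.4 days at 90 kg).
- Change over stay L = −min(13.8, 1.92 × L). Mean daily = change / L. Balance at end = 13.8 + change.

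| ICU stay after randomisation | Mean daily balance (L/day) | Balance at end of stay (L) |
|---|---|---|
| 3 days | −1.92 | +8.0 |
| 5 days | −1.92 | +4.2 |
| 10 days | −1.38 | 0 |
| 14 days | −0.99 | 0 |
| 20 days | −0.69 | 0 |

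A patient still in the ICU on day 5 has a day-5 balance of +4.2 L whatever the later stay.

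**3. Arm level.** Simulation with 25 per arm, 3000 runs and the same daily process in both arms. All of the following are assumptions except the starting mean and SD, which are the planning figures: starting balance mean 13.8 L, SD 7.4 L; −1 L/day for 7 days, then 0; daily SD 1.5 L; 0.05 SARs per ICU day; exponential stays rounded up to whole days, independent of fluid balance. Differences are second arm minus first.

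| Mean stay, first v second arm | Mean daily (L/day) | Rejected | Cumulative (L) | Rejected | SARs in arm |
|---|---|---|---|---|---|
| 10 v 10 days | +0.01 | 4.5% | +0.06 | 5.3% | +0.1 |
| 10 v 7 days | −0.09 | 6.7% | +0.51 | 4.8% | −3.8 |
| 10 v 5 days | −0.15 | 10.3% | +1.13 | 6.4% | −6.1 |
| 7 v 14 days | +0.18 | 12.6% | −0.92 | 7.0% | +8.4 |

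The shorter stay makes the daily mean look better and the cumulative balance look worse, so the two outcomes can point in opposite directions. The fixed day-5 balance was rejected in 4.3% to 4.9% of runs. That benchmark used a day-5 value for every simulated patient, including those whose stay had ended. It shows what a fixed window gives when early exits are handled properly, not that any particular model achieves this.

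**4. Scale.** 6 L over 5 days is 1.2 L/day. The twofold-stay artefacts are 0.15 / 1.2 = 13% and 0.18 / 1.2 = 15% of that for the daily mean, and 0.92 / 6 = 15% and 1.13 / 6 = 19% for the cumulative balance. The expected artefact in the daily mean is proportional to the assumed removal rate. At 1.92 L/day in both arms it would be 0.15 × 1.92 = 0.29 to 0.18 × 1.92 = 0.35 L/day.

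**The case against.** The strongest reply is that nothing decisive rests on these outcomes. Feasibility is judged on day-5 balance, which has a fixed window and two analyses that address death. Mortality and the days-alive outcomes have 90-day windows, so a survival imbalance would be visible beside the secondary results. The ICU stay is also the treatment period, so describing delivery and safety over it is reasonable. All of this stands. It is why the whole-stay outcomes should be kept and the point stays secondary.

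A reader might go further and infer that the daily mean would be wrong by a factor of two: −13.8 / 7 = −1.97 L/day against −13.8 / 14 = −0.99 L/day for the same removal. That compares two hypothetical patients, not two arms, and treats a planning mean without a stated time point as the volume each patient loses. A reader might also infer that the treatment does change length of stay. The documents give no stay data and show no such effect. Nor do they support the inference that a 30% shorter stay gives 30% fewer SARs. The SARs are reactions to furosemide, which can be replaced by renal replacement therapy, and removal ends at neutral, so a constant rate per ICU day is not established.

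The t or Mann-Whitney point concerns the two fluid outcomes. No test is named for the SAR total.

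On the abstract, balance at discharge and balance over the stay coincide for patients discharged alive. The mismatch concerns only those who die in the ICU.

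What remains is that these outcomes mix fluid removal with duration and survival, and the article's death handling does not extend to them.

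**Conclusion.** The point holds as a caution about three secondary outcomes and should be addressed. It does not threaten the primary outcome, the sample size or the feasibility decision.

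The size cannot be determined from the documents. Under the simulated process it is modest: about 0.15 to 0.18 L/day and 0.9 to 1.1 L cumulative with a twofold difference in mean stay, and less with a smaller one. It rests on assumed stays, removal rate and SAR rate, and on stay being independent of fluid balance.

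It also rests on counting the daily mean from randomisation, which Table 1 does not state. Counted from ICU admission, patients who reach neutral score about zero whatever their stay. The dependence on stay then lies in those who leave before neutral, and a shorter stay would look worse rather than better. Either way, the outcome depends on when the stay ends.

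**What to change.** 1. Keep the two whole-stay fluid balances but label them descriptive. Show them with ICU length of stay and ICU deaths by arm, and do not read a t or Mann-Whitney test on them as an effect of fluid removal.
2. For any between-arm comparison of daily balance, use a fixed window from randomisation in the longitudinal model, with the primary outcome's handling of death. Acknowledge that a day 1 to 5 window largely restates the primary outcome.
3. Report SARs over the full ICU stay as the number of patients with at least one and as a rate per ICU patient-day, beside the arm total. Do not cut off at day 5: that would miss later harms and would still fall with early deaths. The rate is itself diluted by days at neutral, so the three figures should be read together.
4. Align the Abstract with Table 1, and state that for ICU deaths the value is the balance at death.

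The cost is some rewording and a little more analysis. Fluid balance is already summarised three times daily on the ICU charts, so no new measurements are needed. The downside is that whole-stay fluid comparisons carry less inferential weight.

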### Monitoring and protocol adhesion

The FFAKI trial is externally monitored according to Good Clinical Practice (GCP) (EU-Directive-2001/20) guidelines including monitoring of consents and source data by external staff.

Protocol adhesion is monitored by the GCP guidelines on the first five patients in both the intervention and control arm at each centre and protocol violations are registered in the CRF of all patients. In case of protocol violations the principle investigator will initiate re-education of participating caregivers.

### Statistical analysis

The main objective of the FFAKI trial is to determine whether the trial intervention is feasible. To capture this we have decided to examine whether the trial intervention leads to a clinically relevant difference in fluid balance after 5 days. This is treated as an interim outcome and in accordance with the newly published Consolidated Standards of Reporting Trials (CONSORT) extension to randomised pilot and feasibility trials [16], we used the standard method of calculating sample size. By including 50 patients in the trial we will have the power to show a difference of 6 L in cumulative fluid balance between groups with a *β* value of 0.80 and a two-sided *α* value of 0.05. The sample size estimation is based upon observational data of patients fulfilling the FFAKI inclusion criteria admitted at our ICU in 2012 and 2013 (mean fluid balance 13.8 L, standard deviation (SD) 7.4 L).

Two complimentary analyses of the primary outcome will be performed in order to account for attrition due to death. In the first analysis the subject-specific fluid balances are modelled in a ‘linear random-effects model’ unconditional on survival status. Difference in fluid balance 5 days after randomisation will be assessed using a Wald test. In the second analysis we will estimate the ‘survival average causal effect’ of the intervention using principal stratification and include a sensitivity analysis to assess the influence of possible violations of assumptions. In both models missing data due to dropout will be handled using ‘inverse probability weighting’.

All parametric data will be presented as mean (SD) and compared using Student’s *t* test. Nonparametric data will be reported as median (interquartile range (IQR)) and compared using the Mann-Whitney *U* test.

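### The described primary analysis names neither fluid balance at randomisation nor site, although the day-5 outcome appears to carry the entry overload and randomisation is stratified by site; adding both terms is a free gain in precision

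*Protocol article*

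**What the plan says.** All references are to the protocol article.

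- **Outcome** (Standard care, and Table 1): "The primary outcome of the FFAKI trial is cumulative fluid balance 5 days after randomisation". The time from which balance accumulates is not spelled out.
- **Entry** (Inclusion criteria): patients must already have a positive balance of at least 10% of ideal body weight.
- **Treatment target** (Resuscitation): "Fluid removal is continued until the patient achieves neutral cumulative fluid balance (±1000 mL".
- **Design** (Methods): the trial is described as a "multicentre, randomised, site-stratified, clinical pilot trial", and "The trial is initiated at three separate centres in Denmark".
- **Primary model** (Statistical analysis): "In the first analysis the subject-specific fluid balances are modelled in a ‘linear random-effects model’ unconditional on survival status". The test follows: "Difference in fluid balance 5 days after randomisation will be assessed using a Wald test". A second analysis estimates the survivor average causal effect by principal stratification. Both use inverse probability weighting for dropout.
- **Other comparisons** (Statistical analysis): a general sentence assigns Student's t test or the Mann-Whitney U test.
- **Sample size** (Statistical analysis): 50 patients for a 6 L difference with 80% power at two-sided 5%, based on "mean fluid balance 13.8 L, standard deviation (SD) 7.4 L" in earlier patients who met the inclusion criteria.

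**The concern.** Fluid can be removed until cumulative balance is neutral only if the count includes what was gained before randomisation. The primary outcome uses the same word, so the day-5 value most likely equals the overload at randomisation plus the change since. The first part cannot be affected by treatment, and it is known for everyone because eligibility depends on it. Left out of the model, its spread counts as noise, and any chance difference between arms in starting overload is carried, to the extent that it persists, into the day-5 difference.

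Site is the stratification factor. If centres differ in fluid practice, stratified allocation removes that source of variation from the true error of the comparison, but an analysis without site still counts it in the estimated error.

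The day-5 difference is the trial's stated test of feasibility and bears on whether a definitive trial is warranted. With about 25 patients per arm and expected losses to death, there is little precision to spare.

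**Working it through.** **Inputs from the article:** N = 50, difference 6 L, SD 7.4 L, two-sided alpha 0.05, power 0.80, three centres.

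**Assumed, because the article does not give them:** 1:1 allocation; within-arm correlation r between balance at randomisation and at day 5 of 0.3 to 0.7; SD of balance at randomisation of 3, 5 or 7.4 L; share q of outcome variance between sites of 5% to 20%; and 40 evaluable patients as an example of attrition.

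**1. The plan's own figure.** For two groups of n, the noncentrality is 6 / (7.4 × √(2/n)). With n = 25 it is 6 / 2.093 = 2.867 on 48 degrees of freedom, and the noncentral t gives power 0.802. The normal approximation gives 24 per arm, 48 in total. The stated 50 is therefore reproduced as the size of an unadjusted two-group t test.

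**2. Adjusting for balance at randomisation.** Residual SD = 7.4 × √(1 − r²). Power is from the noncentral t, with one further degree of freedom spent on the covariate in the adjusted rows.

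| r | Residual SD (L) | Power, N = 50 | Power, N = 40 |
|---|---|---|---|
| 0 (unadjusted) | 7.40 | 0.802 | 0.705 |
| 0.3 | 7.06 | 0.837 | 0.745 |
| 0.5 | 6.41 | 0.900 | 0.822 |
| 0.7 | 5.28 | 0.976 | 0.938 |

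Worked line, r = 0.5, N = 50: 7.4 × √0.75 = 6.41; 6 / (6.41 × √(2/25)) = 6 / 1.813 = 3.31 on 47 degrees of freedom; power 0.900.

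**3. Size of a chance imbalance.** The standard error of the difference in mean balance at randomisation is SD × √(2/25):
- SD 3 L: 0.85 L
- SD 5 L: 1.41 L
- SD 7.4 L: 2.09 L

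The part that reaches day 5 is this difference multiplied by the slope of day-5 balance on balance at randomisation. The target difference is 6 L.

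**4. Leaving out site.** If a share q of the variance lies between sites and allocation is balanced within sites, the actual two-sided alpha is 2 × (1 − Φ(1.96 / √(1 − q))):
- q = 0.05: 0.044
- q = 0.10: 0.039
- q = 0.20: 0.028

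The test is conservative, not inflated.

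**5. Cost of the site terms.** Three centres need two further degrees of freedom. At r = 0.5 and N = 50, even if site explains nothing, power falls only from 0.9000 to 0.8995.

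**The case against.** The strongest objection is that the article is silent on covariates and does not exclude them. It names a linear random-effects model, which could already carry the day-0 value as a response or covariate and site as a term. An article commonly leaves the covariate list to a full protocol or analysis plan. This stands: a reader might infer that the plan fixes a raw, unadjusted day-5 comparison, and the text does not say so. The t and Mann-Whitney sentence does not show it either, because it is a general reporting line and the primary outcome has its own models. What remains is that the section is otherwise specific (model, contrast, test, second estimand, missing-data method), sizes the trial on the unadjusted SD, and makes no use of two variables that the design already supplies.

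Three further inferences also go too far.

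- **Most of the 7.4 L SD is overload present at entry.** The article gives neither the time point nor the components of that SD. The entry floor and the 12-hour window for randomisation may narrow the spread at randomisation, and removal towards neutral balance may weaken the correlation in the experimental arm. The upper end of the power range may therefore be optimistic.
- **The Wald test inflates type I error.** Simulation with a 1.96 cut-off, sandwich standard errors and logistic weights at N = 50 gave 6.1% with no missing data and about 7% with 20-30% missing. The article specifies none of those three choices, and a Wald-type contrast can use a t reference.
- **Ignoring the strata makes the test too liberal.** Step 4 shows the opposite.

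Finally, under randomisation the unadjusted estimate is unbiased, and no stated figure becomes wrong. That also stands.

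**Conclusion.** The point holds as an improvement to the analysis, not as an error in a stated result. The primary outcome very probably includes the overload present at randomisation. This is inferred from the entry criterion and the neutral-balance target, because the article does not define the start of accumulation. The described analysis names neither that baseline nor site. The loss is in precision and in exposure to chance imbalance; there is no bias.

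The power gain in step 2 depends on the assumed correlation, on 1:1 allocation and on a similar correlation in both arms. At the low end (r = 0.3) it is modest, about 0.04 at either sample size. With 40 evaluable patients, adjustment restores power to 0.80 only if r approaches 0.5. If a full analysis plan already includes both terms, a confirming sentence settles the matter.

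**What to change.** 1. State the time from which cumulative balance is counted.
2. Name cumulative balance at randomisation (as a covariate, or as a day-0 response with equal means in the two arms) and site as terms in the linear random-effects model and in the survivor-average-causal-effect analysis.
3. Use the same two terms for the continuous secondary fluid-balance outcomes.
4. Adjust for the baseline; do not replace the outcome by change from baseline. With equal variances, the SD of the change is 7.4 × √(2(1 − r)), which at r = 0.3 is 8.76 L, larger than the unadjusted 7.4 L.
5. As a precaution with at most 50 patients and weighting, base the Wald test on a small-sample reference distribution or report a bootstrap confidence interval.

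This changes analysis wording only. Balance at randomisation is needed to establish eligibility and site is known from the stratification, so no new data are needed and the sample size can stay at 50. The amendment should be dated before the trial statistician is unblinded.
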